# Optimal Dosing and Timing of High-Dose Corticosteroid Therapy in Hospitalized Patients With COVID-19: Study Protocol for a Retrospective Observational Multicenter Study (SELECT)

**DOI:** 10.2196/48183

**Published:** 2023-06-02

**Keywords:** COVID-19, corticosteroid, infectious diseases, virology

## Abstract

**Background:**

In hospitalized patients with COVID-19, the dosing and timing of corticosteroids vary widely. Low-dose dexamethasone therapy reduces mortality in patients requiring respiratory support, but it remains unclear how to treat patients when this therapy fails. In critically ill patients, high-dose corticosteroids are often administered as salvage late in the disease course, whereas earlier administration may be more beneficial in preventing disease progression. Previous research has revealed that increased levels of various biomarkers are associated with mortality, and whole blood transcriptome sequencing has the ability to identify host factors predisposing to critical illness in patients with COVID-19.

**Objective:**

Our goal is to determine the most optimal dosing and timing of corticosteroid therapy and to provide a basis for personalized corticosteroid treatment regimens to reduce morbidity and mortality in hospitalized patients with COVID-19.

**Methods:**

This is a retrospective, observational, multicenter study that includes adult patients who were hospitalized due to COVID-19 in the Netherlands. We will use the differences in therapeutic strategies between hospitals (per protocol high-dose corticosteroids or not) over time to determine whether high-dose corticosteroids have an effect on the following outcome measures: mechanical ventilation or high-flow nasal cannula therapy, in-hospital mortality, and 28-day survival. We will also explore biomarker profiles in serum and bronchoalveolar lavage fluid and use whole blood transcriptome analysis to determine factors that influence the relationship between high-dose corticosteroids and outcome. Existing databases that contain routinely collected electronic data during ward and intensive care admissions, as well as existing biobanks, will be used. We will apply longitudinal modeling appropriate for each data structure to answer the research questions at hand.

**Results:**

As of April 2023, data have been collected for a total of 1500 patients, with data collection anticipated to be completed by December 2023. We expect the first results to be available in early 2024.

**Conclusions:**

This study protocol presents a strategy to investigate the effect of high-dose corticosteroids throughout the entire clinical course of hospitalized patients with COVID-19, from hospital admission to the ward or intensive care unit until hospital discharge. Moreover, our exploration of biomarker and gene expression profiles for targeted corticosteroid therapy represents a first step towards personalized COVID-19 corticosteroid treatment.

**Trial Registration:**

ClinicalTrials.gov NCT05403359; https://clinicaltrials.gov/ct2/show/NCT05403359

**International Registered Report Identifier (IRRID):**

DERR1-10.2196/48183

## Introduction

### Background

The emergence of SARS-CoV-2 in Wuhan caused a global COVID-19 pandemic, with a high mortality and morbidity rate worldwide [1]. Over the past years, many efforts have been made to unravel the underlying complex pathophysiological mechanisms and explore various treatment options. Substantial variation exists in systemic and alveolar levels of inflammation between patients, contributing to the heterogeneous clinical course of the disease. This ranges from asymptomatic infection to life-threatening hypoxemic pneumonia. Corticosteroid therapy has the potential to inhibit disease progression and decrease the severity of clinical symptoms and is first-line immunosuppressive therapy in patients with COVID-19 with hypoxia [2].

The main reason for hospitalization of patients with COVID-19 is the requirement of supplemental oxygen therapy because of hypoxemia. In some patients, ground glass opacification and the beginning of consolidations on pulmonary CT scan are observed [3], accompanied by increased parameters of inflammation and coagulation in bronchoalveolar lavage fluid (BALF) and the systemic compartment [4,5]. In case of progressive respiratory failure, patients with COVID-19 will be admitted to the intensive care unit (ICU). These patients have a significantly decreased partial pressure of oxygen in arterial blood–fraction of inspiratory oxygen concentration ratio and frequently fulfill the Berlin criteria of moderate and severe acute respiratory distress syndrome (ARDS) [6]. Analysis of their inflammatory profiles shows a further elevation of proinflammatory cytokines, which is associated with increased mortality [7,8].

For decades, corticosteroids are given to treat patients with non–COVID-19 ARDS because of their strong anti-inflammatory effects [9]. Among patients with COVID-19, the Randomized Evaluation of Covid-19 Therapy (ie, RECOVERY) study showed that low-dose dexamethasone reduces mortality in patients requiring supplemental oxygen therapy or invasive mechanical ventilation but not in patients without respiratory support [10]. Current COVID-19 guidelines recommend a dose of 6 mg of dexamethasone per day for 10 days when oxygen therapy is required, regardless of the level of inflammation or severity of the disease [2]. Unfortunately, a proportion of patients still show progressive deterioration despite this treatment.

In these dexamethasone-unresponsive patients with COVID-19, corticosteroid therapy is sometimes escalated to a much higher dose. However, large heterogeneity in the type, timing, and dosing of escalated corticosteroid therapy exists [11]. High-dose corticosteroids are mainly administered during the late phase of the clinical course and in patients with the most severe disease, while earlier administration could be beneficial in preventing disease progression. However, the results of the studies on high-dose corticosteroid treatment for critically ill patients with COVID-19 are contradicting [12-15]. A recent meta-analysis compared high-dose corticosteroids versus low-dose corticosteroids in hospitalized patients with COVID-19 and reported no difference in mortality. Given the low level of evidence, inconclusive trial sequential analysis, and substantial heterogeneity, the authors stress the importance of future research to improve the certainty of evidence [16].

Treatment with high-dose corticosteroids may come at the cost of complications, such as secondary infections due to the immunosuppressive effects. To better predict the response to high-dose corticosteroids prior to therapy, additional diagnostic tools such as serum and BALF biomarker determination and whole blood transcriptome analysis could be helpful [17]. Implementation of these tools may result in a more precise and individualized approach to corticosteroid dosing in clinical practice.

Overall, the optimal dosing and timing of high-dose corticosteroids in hospitalized patients with COVID-19 remains uncertain. Here, we present the study design and methodological considerations of the SELECT (Steroids in Hospitalized Patients with COVID-19 in The Netherlands) study, a multicenter study that aims to study the most optimal dosing and timing of corticosteroid therapy to reduce the morbidity and mortality of hospitalized patients with COVID-19. In addition, we aim to provide a basis for personalized corticosteroid treatment regimens by exploring the predictive value of biomarkers and whole blood transcriptome analysis. We hypothesize that the effect of corticosteroid therapy on outcome is determined by the dosage and timing of administration, as well as the patient’s underlying inflammatory state.

### Study Aims

#### Work Package 1: High-Dose Corticosteroid Treatment in the Ward

Work package 1A (WP1A) is used to investigate whether initial treatment with high-dose corticosteroids compared to treatment with 6 mg dexamethasone per day for 10 days, or an equivalent corticosteroid, improves patient outcomes in the ward (Figure 1).

WP1B is used to investigate whether treatment with high-dose corticosteroids compared to no corticosteroids, after treatment with 6 mg dexamethasone per day for 10 days, improves patient outcomes in the ward.

**Figure 1 figure1:**
[figure not shown]
Integration of work packages in the Steroids in Hospitalized Patients with COVID-19 in The Netherlands (SELECT) study. On the y-axis, the viral and host inflammatory response are depicted. On the x-axis, the admission to the ward or intensive care unit (ICU) is shown, and below that, the World Health Organization (WHO) clinical progression scale is displayed as a measure of supplemental oxygen therapy. steroids: corticosteroids; HDS: high-dose corticosteroids; WP: work package.

#### Work Package 2: High-Dose Corticosteroid Treatment in the ICU

Work package 2 (WP2) is used to investigate whether initial treatment with high-dose corticosteroids compared to treatment with 6 mg dexamethasone per day for 10 days, or an equivalent corticosteroid, improves patient outcomes in the ICU.

#### Work Package 3: High-Dose Corticosteroid Treatment After Standard Corticosteroid Treatment in the ICU

Work package 3 (WP3) is used to investigate whether treatment with high-dose corticosteroids compared to no corticosteroids, after treatment with 6 mg dexamethasone per day for 10 days, improves patient outcomes in the ICU.

#### Work Package 4: Biomarker Profiles and Whole Blood Genome Transcriptomes in High-Dose Corticosteroid Treatment

Work package 4a (WP4a) is used to investigate whether biomarker profiles in serum and BALF act as response predictors for high-dose corticosteroids on the outcome.

WP4b is used to investigate whether whole blood transcriptome analysis acts as a response predictor for high-dose corticosteroids on the outcome.

## Methods

### Definition High-Dose Corticosteroids

High-dose corticosteroids are defined as every treatment with dexamethasone >6 mg daily or an equivalent corticosteroid (Table 1). Regarding prior and continuing use of corticosteroids for other conditions, corticosteroids are considered as part of the COVID-19–related intervention when the high-dose threshold is passed.

**Table 1 table1:** Equivalent corticosteroids and dosages (total daily dosing)^a^.

Drug	Equivalent dose (mg)	Low-dose (mg)	High-dose (mg)
Dexamethasone	0.75	≤6	>6
Cortisone	25	≤200	>200
Hydrocortisone	20	≤160	>160
Prednis(ol)one	5	≤40	>40
Methylprednisolone	4	≤32	>32
Bethamethasone	0.75	≤6	>6

^a^This table shows the equivalent corticosteroids and dosages. The equivalent dose is derived from Farmacotherapeutisch Kompas [18].

### Study Design and Setting

The SELECT study is a retrospective cohort study with data from 22 hospitals in the Netherlands, including 4 academic and 18 nonacademic hospitals (Figure 2). Other hospitals may be included as the study progresses and we will use routinely collected electronic data from the participating hospitals. The data sets will contain data on hospitalized patients with COVID-19 from the date the first patient was admitted to the hospital in the Netherlands (March 1, 2020) until data transfer (expected May-December 2023). We will use the heterogeneity in therapeutic regimens in time (ie, first, second, and third epidemiological wave), centers (per protocol high-dose corticosteroids or not), and individual patients in the initial databases to address our aims. In a subpopulation of patients, we will use biobank material collected within the Collaboration on Identification, Understanding and Improved Management of patients with infectious diseases study of the Erasmus MC or collected at the Amsterdam University Medical Center (UMC) within the MERMAIDS-ARI, VIS cohort study or the Amsterdam UMC COVID-19 biobank.

**Figure 2 figure2:**
[figure not shown]
Participating hospitals of the Steroids in Hospitalized Patients with COVID-19 in The Netherlands (SELECT) study. UMC: University Medical Center. MC: Medical Center; OLVG: Onze Lieve Vrouwe Gasthuis.

### Patient Selection and Inclusion Criteria

Adult patients (≥18 years) hospitalized with polymerase chain reaction–confirmed COVID-19 or high clinical suspicion of COVID-19 will be included (Figure 3). Pregnant patients and patients receiving corticosteroids for other conditions during or prior to hospital admission are eligible, although a prespecified sensitivity analysis excluding these patients will be performed. Patients who die within 48 hours after admission or patients who object to participate will be excluded from the study. In WP1 and WP4, we will include patients from all SARS-CoV-2 epidemic waves, and in WP2-3, we will include patients from the first and second waves only. Specific inclusion and exclusion criteria for each work package will be applied. In WP1A, patients will be included who are admitted to the ward with a World Health Organization clinical progression scale class of 4-5 [19] (ie, no oxygen or oxygen therapy via a cannula or [non-rebreather] mask). WP1B includes patients who have progressed to the World Health Organization clinical progression scale class of 5-6 (ie, noninvasive oxygen therapy, including conventional oxygen via cannula [non-rebreather] mask, high-flow nasal cannula, noninvasive continuous positive airway pressure, and noninvasive bilevel positive airway pressure) after in-hospital treatment with 10 days of 6 mg per day dexamethasone. The study population for WP2-4 consists of patients admitted to the ICU for a period exceeding 48 hours, who received invasive mechanical ventilation via an endotracheal tube, a tracheostomy, or extracorporeal membrane oxygenation during their ICU stay.

**Figure 3 figure3:**
[figure not shown]
Patient inclusion. World Health Organization (WHO) classification: 0=uninfected, 1=asymptomatic; viral RNA detected, 2=symptomatic; independent, 3=symptomatic; assistance needed, 4=hospitalized; oxygen by mask or nasal prongs, 5=hospitalized; oxygen by mask or nasal prongs, 6=hospitalized; oxygen by noninvasive ventilation or high flow, 7=intubation and mechanical ventilation partial pressure of oxygen in arterial blood–fraction of inspiratory oxygen concentration (PaO2/FiO2) ratio of ≥150, 8=mechanical ventilation PaO2/FiO2 ratio of <150 or vasopressors, 9=mechanical ventilation PaO2/FiO2 ratio of <150 and vasopressors, dialysis or extracorporeal membrane oxygenation, 10=dead. PCR: polymerase chain reaction; WP: work package.

### Ethics Approval and Consent to Participate

The study will be conducted according to the principles of the Declaration of Helsinki (64th World Medical Association General Assembly, Fortaleza, Brazil, October 2013) and in accordance with Erasmus MC Research code, Netherlands Code of Conduct for Research Integrity, General Data Protection Regulation, Code of Conduct for Health Research (not subjected to the Medical Research Involving Human Subjects Act [non-WMO]), Code of Conduct for Responsible Use of Human Tissue (Non-WMO), and Medical Treatment Contracts Act. The study was approved by the Medical Research Ethics Committee from Erasmus University Medical Center (MEC-2022-0297) and the local review boards of all other participating centers. Regarding informed consent procedure: within the Erasmus MC, a consent waiver was provided by the Medical Research Ethics Committee for research including patients with COVID-19 due to the pandemic (exception due to emergency situation). Therefore, an opt-out informed consent procedure will be used in the participating centers, and subjects with registered objections to participate will be excluded from the study. This opt-out registration method was approved by the Medical Research Ethics Committee from Erasmus University Medical Center (MEC-2022-0297). Each center is responsible for appropriate informed consent procedures, which are covered in the data transfer agreements. Regarding the biobank data, only biobank material collected within the Collaboration on Identification, Understanding and Improved Management of patients with infectious diseases study of the Erasmus MC (METC number primary application: 2017-0417 and amendment 2020-0222) and samples collected at the Amsterdam UMC within the MERMAIDS-ARI (NL54834.018.15), VIS cohort study (NL73759.018.20), and the Amsterdam UMC COVID-19 biobank will be used.

### Data Collection

In WP1, variation in corticosteroid treatment protocols on the ward between centers is evaluated via questionnaires and extraction of data from the electronic patient record. The focus lies on collecting data from centers that use high-dose corticosteroids on the ward directly after admission and subsequently collecting data from centers with low-dose regimens as a comparison. For the data collection of ICU patients (WP2-3), a collaboration with 2 large COVID-19 study groups is started: the Practice of Ventilation in COVID-19 study (ie, PROVENT-COVID) study and the “Practice of Adjunctive Treatments in Intensive Care Unit Patients with Coronavirus Disease 2019” (PROACT-COVID) study [20,21]. The data of interest will be collected in Castor EDC [22], and it will be imported from each center via a secured data transfer system. Corticosteroid data will be collected on a daily basis including type, dose, and administration route. Regarding biobank WP4, a number of serum biomarker levels were already determined during standard COVID-19 care. In case of missing measurements, the stored samples (Tempus tubes) in the biobank can be used. The BALF was collected during routine COVID-19 care in the Amsterdam University Medical Centers and saved in aliquots at −80 °C for further analysis. SARS-CoV-2 viral load will be measured in BALF by using an in-house reverse transcription polymerase chain reaction. Subsequently, other commercially and generally available biomarkers might be determined in serum and BALF later by using a multiplex assay, such as Luminex. For the whole genome transcriptomes analysis, material was collected and saved in blood RNA Tempus tubes.

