### Statistical Analysis

Data will be analyzed on a convenience sample. No sample size calculations are considered for the study nor will they be provided post hoc [23]. The use of high-dose corticosteroids will be defined as a dichotomous variable (yes or no) in primary analysis and as a continuous variable in secondary analysis.

To study between-center variation in corticosteroid dosing strategy, the proportion of individuals who received high-dose corticosteroids will be compared across hospitals. Determinants of receiving high-dose corticosteroids will be evaluated using a multivariable logistic regression model with study center forced in the model. Whether the effects of significant determinants are different across centers will be tested through a determinant × center interaction term added for each determinant, separately.

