Regarding WP4, patients are randomly selected and cases will be patients treated with high-dose corticosteroids, whereas controls will be patients who were not treated with high-dose corticosteroids. In WP4a, inverse probability treatment weighting and inverse probability of censoring weights will be used together in a marginal structural model. After we have analyzed the effect of high-dose corticosteroids on mortality and the other outcome measures, we will use this model to determine if the listed biomarkers modify the effect of high-dose corticosteroids on mortality.

In WP4b, we will identify transcriptome features that are differentially altered between cases and controls. Mean transcriptome levels will be compared using an unpaired *t*-test and *P* values will be adjusted for false-discovery rate using the Benjamini-Hochberg procedure. The log_2_ mean fold change of levels between cases and controls will also be calculated for each transcriptome. We will define transcriptome features as those with an adjusted *P* value of <.05 and a >2.0 or <–2.0 log_2_ mean fold change in level.

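### The Data Collection section names Tempus tubes as the back-up for missing serum biomarkers, yet identifies them as blood RNA tubes, while WP4a needs serum levels

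*Protocol article*

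**What the plan says.** The aim of work package 4a (WP4a), under Study Aims, is to "investigate whether biomarker profiles in serum and BALF act as response predictors for high-dose corticosteroids on the outcome". The Statistical Analysis section puts these markers into a weighted marginal structural model: once the treatment effect has been analysed, "we will use this model to determine if the listed biomarkers modify the effect of high-dose corticosteroids on mortality".

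The Data Collection section describes where the values come from, in this order:

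- Routine care: "Regarding biobank WP4, a number of serum biomarker levels were already determined during standard COVID-19 care".
- Back-up, in the next sentence: "In case of missing measurements, the stored samples (Tempus tubes) in the biobank can be used".
- Lavage fluid: kept as aliquots at −80 °C, with viral load to be measured in it.
- Later assays: "other commercially and generally available biomarkers might be determined in serum and BALF later by using a multiplex assay, such as Luminex".
- Transcriptome work: "For the whole genome transcriptomes analysis, material was collected and saved in blood RNA Tempus tubes".

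The only stored specimens that the section describes are the lavage aliquots and the Tempus tubes. It describes no stored serum tube or aliquot.

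**The concern.** The back-up sentence follows directly on a sentence about serum biomarker levels, so the missing measurements it speaks of are naturally read as serum measurements. The specimen it names is the one that the same section assigns to RNA work. A blood RNA tube and a serum sample are different specimens, and nothing in the article says that a marker level from one can stand in for a level from the other.

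What is at stake is the comparability of serum marker values within WP4a. If some patients have a routine serum value and others a value from a different matrix, both enter the model as one variable. A systematic difference between matrices would then act as measurement error in the effect modifier. That error need not be random. Values are filled only where routine care left a gap, so the type of specimen may follow who was tested, in which hospital and when. The interaction between that marker and high-dose corticosteroids could be distorted as a result.

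**Working it through.** The plan gives no figure on this point to reproduce, so the main check is to set the statements side by side.

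1. **Specimen required.** Study Aims (Work Package 4) and Statistical Analysis: serum and lavage markers, used as effect modifiers.
2. **Specimen named as back-up for missing values.** Data Collection: stored Tempus tubes.
3. **What those tubes are.** Data Collection, four sentences later: blood RNA tubes for the transcriptome analysis, which is WP4b.
4. **Specimen for later assays.** Data Collection, between items 2 and 3: serum and lavage fluid.

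Items 1 and 4 call for serum. Items 2 and 3 together supply an RNA tube. Item 2 cannot be taken literally and still agree with items 1 and 4.

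**Scope.** Only serum markers with at least one missing value can be affected. Lavage markers have their own aliquots. Study Design and Setting says that biobank material covers part of the cohort only ("In a subpopulation of patients, we will use biobank material collected within the Collaboration on Identification, Understanding and Improved Management"). The article gives neither the number of WP4a patients nor the share with missing serum markers. Nor is there a planning figure to set this against: "No sample size calculations are considered for the study nor will they be provided post hoc". The share filled from Tempus tubes could lie anywhere from 0% to 100%.

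**Illustration, on assumed inputs only.** Let the true marker X have mean 0 and variance 1. Suppose a fraction m of values is replaced, independently of X, to give X*. In a linear model the slope shrinks by the factor Cov(X*, X) / Var(X*).

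- *Replaced values are noise of equal variance.* Cov = 1 − m and Var = 1, so the factor is 1 − m. For m = 10% to 40% (assumed) it is 0.90 to 0.60.
- *Replaced values all read d standard deviations below the mean.* Cov = 1 − m and Var = (1 − m) + m·d² − m²·d² = (1 − m)(1 + m·d²), so the factor is 1/(1 + m·d²).
  - m = 0.1, d = 2: 1/1.4 = 0.71
  - m = 0.3, d = 2: 1/2.2 = 0.45
  - m = 0.3, d = 3: 1/3.7 = 0.27
- *No values replaced.* m = 0 and the factor is 1 in both cases.

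These factors show that pooling matrices can matter. They do not estimate the effect in this study: m and d are not in the article, the formula is for a linear slope with replacement independent of X, and WP4a uses a weighted model with an interaction on mortality.

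**The case against.** The best defence is that the parenthesis is a slip. The plan to run a multiplex assay later in serum suggests that stored serum exists, and the back-up sentence may simply carry the wrong label. No WP4a value would then be affected. The wording is also permissive: the samples can be used, and the article describes neither a serum assay on RNA material nor a rule for pooling the results. Finally, specimen handling is detail that a condensed article may leave to the full protocol.

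The first two points stand, and they limit what can be claimed. The third does not remove the point. The article does not leave the specimen open; it names one, and the one it names conflicts with the same section. A slip would need the same correction.

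A reader might go further and infer that missing values will be filled from RNA tubes and that WP4a is invalid for every such patient. The article does not support this. It does not say that such assays will be run, and it says nothing about what the tube does to a protein measurement.

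Four other inferences also fail:

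- The interaction is not WP4a's only result, because the treatment effect on mortality and the other outcomes is analysed first.
- Not every WP4a marker is exposed, because lavage markers and fully measured serum markers are untouched.
- The list of blood markers under Statistical Analysis is the covariate list for work packages 1 to 3. The article does not say that it is the WP4 list.
- Depletion of RNA material for WP4b cannot be argued without tube counts or volumes, and none are given.

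**Conclusion.** The point holds as an inconsistency in a stated specimen rule. The Data Collection section offers Tempus tubes for missing serum markers and identifies the same tubes as blood RNA tubes, while WP4a is defined on serum and lavage levels.

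Any harm to the analysis is conditional on two things: that serum markers are in fact assayed in those tubes, and that the results are pooled with routine serum values. In that case the affected serum markers would mix two matrices, and their interaction with treatment could be distorted. The extent is unknown and may be nil. The contradiction itself rests on the article's own words and needs no assumption about tube chemistry. It is worth correcting because the correction is cheap and the sentence, followed literally, would supply the wrong specimen.

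**What to change.** In the Data Collection section:

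1. Replace the parenthesis naming Tempus tubes with the stored serum specimen, and say which of the named biobanks holds it.
2. State that Tempus tubes are reserved for the WP4b transcriptome analysis.
3. State that a marker value obtained from a different matrix will not be pooled with routine serum values in WP4a, and that the value is left missing when no stored serum exists.

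The cost is a change of wording and a check of the biobank inventory. The downside is that patients without stored serum contribute no measured value for that marker, which reduces the information in WP4a by an amount that the inventory check would show.
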